#### Rationale

Using established questionnaires and scales, the methodology of this protocol only focuses on clinical and patient-reported outcomes, including pain, urinary incontinence, sleep quality, and activities of daily life.

## Statistical methods

### Statistical methods for primary and secondary outcomes {20a}

#### Characteristic statistics

Frequencies and percentages will be used to summarize qualitative data, such as demographic factors.

The mean ± standard deviation will be used to express quantitative data, including ratings from the visual analogue scale, incontinence severity index, Pittsburgh Sleep Quality Index, and Barthel Index Scale.

#### Comparisons within the group (before and after the intervention)

If the data are normally distributed, the paired *t*-test will be employed.

If the data are not normally distributed, the Wilcoxon signed-rank test will be applied.

#### Comparisons between groups (Mitchell’s vs. Benson’s relaxation)

For data that is regularly distributed, the independent *t*-test will be employed.

Mann–Whitney for data that is not typically distributed, the *U* test will be applied.

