### Sample size {14}

#### Sample size: calculation for comparing two means at pain severity using VAS

##### Formula used

The formula for calculating the sample size for comparing two means is:$$n\geq\left[\left(Z\_\left\{1-\alpha/2\right\}+Z\_\left\{1-\beta\right\}\right)^2\cdot\left(\upsigma_1{}^2+\upsigma_2{}^{2/r}\right)\right]/\left(\mu_2-\mu_1\right)^2$$where:*Z*_{1-*α*/2} is the *Z*-score corresponding to the two-sided significance level.*Z*_{1-*β*} is the *Z*-score corresponding to the desired power.σ_1_^2^ and σ_2_^2^ are the variances of the two groups.*r* is the ratio of the group sizes.(*μ*_2_—*μ*_1_) is the difference in means between the two groups.Alpha (*α*): 0.05 (significance level) = 1.96Beta (*β*): 0.2 (power = 1—*β* = 0.8) = 0.084Mean in group 1 (*μ*_1_): 7.916 (A s per reference article)Standard deviation in group 1 (σ_1_): 2.256Mean in group 2 (*μ*_2_): 5.983Standard deviation in group 2 (σ_2_): 2.327Ratio of group sizes (group 2/group 1): 1:1

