## Data collection and management

### Plans for assessment and collection of outcomes {18a}

Baseline assessment: Before giving any intervention, data will be collected from subjects at the beginning of the first week.Intervention period: During the 4 weeks of the intervention, subjects will get both the relaxation technique (Benson’s and Mitchell’s), along with the conventional physiotherapy exercises.Post-intervention assessment: After the fourth week of intervention, right after the intervention period, data will be gathered once again.

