#### Rationale

According to this protocol, the procedure does not specify any plans or techniques for further studies, such as adjusted or subgroup analysis.

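### The group comparison is an unadjusted test chosen by the shape of the data, with week-4 or change score left open; a pre-specified baseline-adjusted model would fix the target at almost no cost

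*Protocol article*

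**What the plan says.** All references are to the Protocol article.

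- **Test.** Under Comparisons between groups, within Statistical methods {20a}: "For data that is regularly distributed, the independent *t*-test will be employed". For other data a Mann–Whitney U test replaces it. No criterion for normality is given, no covariate is named, and the section does not say whether the compared variable is the week-4 score or the change from baseline.
- **Adjustment.** Methods for additional analyses {20b} is marked not applicable. Its rationale says that "the procedure does not specify any plans or techniques for further studies, such as adjusted or subgroup analysis".
- **Baseline data.** Plans for assessment and collection of outcomes {18a} says: "Before giving any intervention, data will be collected from subjects at the beginning of the first week". A second assessment follows after week 4. The Discussion confirms that VAS, ISI, PSQI and Barthel are all taken at both times.
- **Use of baseline.** The only stated use is in the within-group paired tests in {20a}.
- **Sizing.** Sample size {14} compares two mean VAS levels using the full standard deviations, with no baseline correlation, and arrives at 23 per group.

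**The concern.** The objective is to find which of two randomised techniques does better, so the between-group comparison carries the trial. Two things about it stay open until the data are seen.

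The first is the test. A t-test estimates a difference in means, while Mann–Whitney addresses whether values in one arm tend to exceed those in the other. If the look of the data decides between them, the target of inference is not fixed in advance. With about 23 women per arm, any check of normality is also imprecise.

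The second is the response variable. Week-4 scores and change scores can give different answers when baselines differ by chance, and their power can differ widely. If week-4 scores are compared, the baseline measurement does no work in the group comparison. If change is compared, baseline enters with a fixed coefficient of one, which is inefficient unless the correlation is high. At stake are precision that could be had almost free and an avoidable degree of analyst discretion on the main result.

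**Working it through.** **Inputs, from Sample size {14}.** Mean VAS in group 1 is "7.916 (A s per reference article"); the group 2 mean is 5.983; the SDs are 2.256 and 2.327; allocation is 1:1; alpha is 0.05, with the Z-score "corresponding to the two-sided significance level"; power is 0.80. The difference is 7.916 − 5.983 = 1.933. The root-mean-square SD is √[(2.256² + 2.327²)/2] = √(10.504/2) = 2.292.

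**Assumptions not in the document.** The baseline/week-4 correlation ρ is not given, so a range is shown. The stated SDs are taken to apply to week-4 scores and, for change scores, to baseline as well. All 23 women per arm are taken to complete.

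**Step 1: reproduce the plan's figure.** n = (1.960 + 0.842)² × 10.504 / 1.933² = 22.07, rounded up to 23 per arm and 46 in total. This agrees with the plan. The value printed for the power quantile, 0.084, would give 11.7, so the calculation evidently used 0.84.

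**Step 2: power of the unadjusted t-test on week-4 scores.** The standard error is 2.292 × √(2/23) = 0.676 and the noncentrality is 1.933/0.676 = 2.86. On 44 df, power is 0.799 (0.816 by the normal approximation). The planned 80% is delivered.

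**Step 3: alternatives at the same 23 per arm.** ANCOVA replaces the SD by SD × √(1 − ρ²), on 43 df. The change-score t-test replaces it by SD × √[2(1 − ρ)], on 44 df. For example, at ρ = 0.5 the ANCOVA SD is 2.292 × 0.866 = 1.985. At ρ = 0.3 the change-score SD is 2.292 × 1.183 = 2.712.

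| ρ (assumed) | t-test, week 4 | ANCOVA | t-test, change |
|---|---|---|---|
| 0 | 0.799 | 0.798 | 0.507 |
| 0.1 | 0.799 | 0.802 | 0.550 |
| 0.3 | 0.799 | 0.834 | 0.657 |
| 0.5 | 0.799 | 0.898 | 0.799 |
| 0.7 | 0.799 | 0.975 | 0.951 |

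ANCOVA exceeds the change-score test in every row. Against the week-4 t-test it gains nothing near ρ = 0, about 3.5 points at 0.3, 10 at 0.5 and 18 at 0.7.

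**Step 4: the normality switch, by simulation.** There were 2,500 trials per setting. The switch was assumed to be a Shapiro–Wilk test at 0.05 in either arm, since the plan gives no rule.

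- *Normal data.* The Mann–Whitney branch was taken in about 10% of trials. The type I error of the two-stage rule was 0.049 to 0.053.
- *Strongly skewed data (gamma, shape 1.5).* That branch was taken in about 93% of trials, and type I error was 0.044 to 0.049. Mann–Whitney power was 0.90 to 0.91. ANCOVA on the raw scale had 0.80, 0.81, 0.89 and 0.95 at ρ = 0, 0.3, 0.5 and 0.7. Mann–Whitney is therefore ahead up to about ρ = 0.5, and ANCOVA is ahead at 0.7.

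**The case against.** The strongest reply is that the plan is coherent as it stands. The trial was sized for two means, a t-test on week-4 scores gives the planned power, and randomisation makes the unadjusted comparison unbiased, with chance imbalance already reflected in its standard error. The article may also leave the normality rule and the exact response variable to a statistical analysis plan that is not shown. All of that is fair, and the missing normality criterion alone would not be a finding. What remains is a choice the article does state: an unadjusted test, switched by the data, with no adjusted analysis planned.

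Several stronger readings are tempting but not supported.

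- *The baseline is thrown away.* The response variable is not named. If change is tested, baseline is used, and the paired tests use it in any case. Sizing on mean levels makes a week-4 comparison the likelier reading, but that is an inference.
- *Adjustment is ruled out.* The text under {20b} reports that none is specified. It does not forbid a baseline covariate.
- *ANCOVA always has more power.* This depends on a correlation the document does not give. It may be low here, because baseline is early postoperative pain and the endpoint comes after four weeks of intervention. Under strong skew with low to moderate correlation, the comparison with Mann–Whitney reverses.
- *Baseline imbalance passes straight into the result.* For week-4 scores it carries over only in proportion to ρ: with equal SDs, a 1-point imbalance at ρ = 0.3 shifts the estimate by about 0.3. Any probability of such an imbalance would also require taking the sample-size SD as the baseline SD, and the protocol does not say at what time point that SD was measured.
- *The switch inflates type I error.* The simulation shows no sign of this.

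**Conclusion.** The point holds as an improvement the trial can make almost free, not as an error that invalidates the design. The between-group analysis leaves the target of inference to the observed data and the response variable unstated, and it makes no efficient use of a baseline that is collected anyway.

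With the protocol's inputs, a baseline-adjusted model for VAS keeps power at 0.80 if the correlation is negligible and raises it to 0.83 to 0.975 for correlations of 0.3 to 0.7. If change scores were chosen instead, power would be below the planned 80% for correlations under about 0.5, and as low as 0.51 at zero. These figures assume 23 completers per arm, roughly normal scores, and the stated SDs at the relevant time points. The power gain is usual but not guaranteed. The gain in having one fixed estimand does not depend on the correlation.

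The VAS figures do not carry over to ISI. Outcomes {12} makes it a second primary outcome and describes it as sorting incontinence into severity categories, so a linear model is not automatically suitable for it.

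**What to change.** Before any analysis, name the response variable and one baseline-adjusted analysis for each outcome:

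- **VAS (primary):** linear model of week-4 VAS on randomised group and baseline VAS, reporting the adjusted mean difference with its 95% CI.
- **ISI (primary):** proportional-odds model of the week-4 category on group and baseline ISI.
- **PSQI:** as for VAS.
- **Barthel:** a baseline-adjusted ordinal or rank-based model, with the choice named in advance.

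Remove the normality switch. Keep the Mann–Whitney test, or a permutation test, as a stated sensitivity analysis whatever the distribution looks like. Adding type of LSCS (emergency or elective) as a covariate is optional.

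The cost is a change of analysis wording. Sample size, visits and data collection stay as they are. The statistical price is one degree of freedom, which at zero correlation lowers VAS power from 0.799 to 0.798.

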### Interim analyses {21b}

Not applicable.

#### Rationale

This protocol does not mention conducting any intermediate analyses during the trial. Data will be gathered at baseline (pre-intervention) and at the conclusion of the 4-week intervention period (post-intervention), according to the study design. All statistical analyses must be carried out following the conclusion of data collection.

### Methods for additional analyses (e.g., subgroup analyses) {20b}

Not applicable.

#### Rationale

According to this protocol, the procedure does not specify any plans or techniques for further studies, such as adjusted or subgroup analysis.

### Methods in analysis to handle protocol non-adherence and any statistical methods to handle missing data {20c}

Not applicable.

For subjects who finish the research, the protocol mainly concentrates on pre- and post-intervention analyses, and all analyses are designed for participants who finish the pre- and post-intervention questionnaires.

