### Criteria for discontinuing or modifying allocated interventions {11b}

At any time, participants may request to stop or alter the intervention they have been assigned, or the investigator may decide that they should stop or alter the intervention if they suffer any discomfort, an adverse event, or a worsening of their condition.

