### Plans to promote participant retention and complete follow-up {18b}

#### Daily follow-up

To keep subjects engaged and track adherence, they will be contacted every day throughout the intervention period.

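### Every analysis is limited to women who complete both questionnaires, and the protocol does not say that women who stop the technique are still assessed at week 4, so outcome-related loss that differs by arm can bias the comparison.

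*Protocol article*

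**What the plan says.** - **Analysis population.** Section {20c} declares the item on non-adherence and missing data not applicable, then gives a rule: "all analyses are designed for participants who finish the pre- and post-intervention questionnaires". The rule covers both primary outcomes (VAS, ISI) and both secondary outcomes (PSQI, Barthel).
- **Stopping the technique.** Under section {11b}, "participants may request to stop or alter the intervention they have been assigned" at any time, with no reason required. Separately, the same section gives the investigator discretion to "stop or alter the intervention if they suffer any discomfort, an adverse event, or a worsening of their condition".
- **Outcome timing.** Section {18a} sets a single assessment after baseline: "After the fourth week of intervention, right after the intervention period, data will be gathered once again".
- **Retention.** Section {18b} plans daily contact ("they will be contacted every day throughout the intervention period") and names baseline and the end of week 4 as retention checkpoints.
- **Blinding and delivery.** Section {17a} blinds the outcome assessor. The principal investigator enrols and assigns women ({16c}) and gives or oversees sessions in hospital ({11c}).

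**The concern.** Two rules meet without anything to join them. One admits only women with both questionnaires. The other expects some women to stop treatment, and the investigator's listed reasons lie close to what the four outcome scales measure. The investigator also knows the arm, so stopping could differ between arms.

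With only one assessment after baseline, a woman who misses it contributes nothing to the comparison. If one technique is less well tolerated and the women who do badly on it are not assessed at week 4, the women left in that arm look better than the arm really did. The contrast would then no longer be between the groups as randomised. With 23 women per arm, the loss of one or two matters.

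This is not a detail that an unseen analysis plan would settle. The article itself fixes the population, and an analysis plan that followed it would carry the same restriction.

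**Working it through.** **Inputs from the protocol (section {14}).** VAS means 7.916 and 5.983; SDs 2.256 and 2.327; alpha 0.05 ("corresponding to the two-sided significance level"); power 0.80; ratio 1:1. No dropout rate or allowance is given.

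**Step 1: the plan's own figure.**
- Difference: 7.916 − 5.983 = 1.933.
- Sum of variances: 2.256² + 2.327² = 10.504. Common SD: √(10.504/2) = 2.292.
- n per group = (1.960 + 0.842)² × 10.504 / 1.933² = 22.07, rounded up to 23, so 46 in total. This matches the protocol. The result is the bare formula value, with no allowance for loss.

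**Step 2: worst-case shift in one arm.** Assume normal, uncapped scores and that exactly the worst fraction q of one arm is lost. The mean of the remaining women falls by SD × φ(z) / (1 − q), where z is the (1 − q) normal quantile and φ the normal density.

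| q (assumed) | φ(z) | Shift in mean VAS | Share of 1.933 |
|---|---|---|---|
| 5% | 0.103 | 0.25 | 13% |
| 10% | 0.175 | 0.45 | 23% |
| 15% | 0.233 | 0.63 | 33% |
| 20% | 0.280 | 0.80 | 41% |

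**Step 3: effect on the test.** This is a simulation of 23 vs 23 women, SD 2.292, independent t-test, 40,000 runs, no true difference.

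| Worst scores lost | Bias towards that arm | Type I error |
|---|---|---|
| none | about 0 | 4.9% |
| 1 of 23, one arm | 0.20 | 6.7% |
| 2 of 23, one arm | 0.37 | 9.7% |
| 3 of 23, one arm | 0.53 | 13.8% |
| 5 of 23, one arm | 0.83 | 24.7% |
| 2 of 23 in each arm | 0.003 (simulation noise) | 7.6% |

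If the planned difference of 1.933 is real and the truly worse arm loses its worst 2 women, the estimate shrinks to about 1.56 and power falls from about 80% to about 64%. With 5 lost, the figures are about 1.11 and 39%.

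**Step 4: how far the worst case overstates.**
- *Weaker selection.* If a normal propensity to leave correlates 0.3 to 0.5 with the score (assumed), the shift is multiplied by that correlation. At 10% loss: 0.3 × 0.45 = 0.13 to 0.5 × 0.45 = 0.22 points.
- *Capped scale.* With mean 7.916 and SD 2.256, about 18% of normal scores would exceed 10. If the VAS runs from 0 to 10 (assumed) and scores are capped there, losing the worst 10% shifts the mean by 0.26 points. For the group with mean 5.983 it is 0.41.
- *Equal loss.* The last row of step 3 shows almost no bias in the mean difference. The type I error still rises somewhat, because cutting the upper tails makes the observed SD too small.

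**The case against.** The strongest reply is that section {20c} defines the analysed set by completed questionnaires, whereas section {11b} concerns stopping the intervention. A woman who stops the technique but answers at week 4 is a completer and stays in the analysis. This stands. A reader might infer that the rule itself removes women who stop treatment, or that the randomised comparison is necessarily lost. The documents do not say so: nobody is excluded for non-adherence as such. What remains is that no section says women who stop will be assessed.

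A reader might also infer that nothing keeps these women in follow-up. That is not supported. Section {18b} plans daily contact and a week-4 checkpoint, and neither is limited to women still practising the technique. This reduces the likely loss, but the article describes the contact as a means of engagement and of tracking adherence, and it leaves the analysis population as it is.

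Third, the reasons tied to outcome belong to the investigator's decision only. A participant's request needs no reason, so it cannot be assumed to be outcome-related.

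Finally, the 0.45 and 0.80 point shifts could be read as the expected bias. They are not. They assume loss in one arm only, perfect selection and uncapped scores, and no dropout rate is documented.

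**Conclusion.** The point holds as a risk of bias, not as a demonstrated bias. The protocol fixes a completers-only analysis for every outcome, calls missing data and non-adherence not applicable although it provides for stopping treatment, and does not require week-4 assessment of women who stop. Bias in the mean difference needs loss that is related to outcome and that differs between arms; both are possible here, and neither is established.

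The size cannot be found from the documents. Under the worst-case assumptions of step 2, 10% or 20% loss moves one arm's mean VAS by 0.45 or 0.80 points, 23% or 41% of the planned difference. Realistic selection or a capped scale gives less, and equal loss gives almost none. The change is still worth making before data collection ends, because a missed week-4 assessment cannot be recovered later.

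**What to change.** 1. **Sections {18a} and {20c}.** State that every randomised woman is assessed at week 4 on VAS, ISI, PSQI and Barthel, whether or not she stopped or altered the technique, and that all women are analysed in the group assigned. Remove the statement that the item is not applicable.
2. **Women who do not attend.** Allow remote collection by the blinded assessor named in section {17a}, not by whoever makes the daily contact, unless that is the same blinded person. Specify a pain score that works by telephone, since a visual scale cannot be marked that way.
3. **Main analysis.** Use a baseline-adjusted comparison and bring sections {20a} and {20b} into line with it. With a single visit after baseline, imputing week-4 scores from baseline and arm adds little to this model, so multiple imputation is not essential.
4. **Sensitivity analysis.** Add one in which missing week-4 scores are assumed worse than observed, by amounts fixed in advance.
5. **Reporting.** Give withdrawals, with reasons, by arm.

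The cost is a change of wording, a few remote assessments and a little more analysis. The daily contact that makes follow-up feasible is already planned.

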### Plans to give access to the full protocol, participant-level data, and statistical code {31c}

#### Full protocol

No clear strategy for public access outside of the criteria for publishing and trial registration.

#### Participant level data

No intention to share.

#### Statistics code

No intention to share.

## Oversight and monitoring

### Composition of the coordinating center and trial steering committee {5d}

#### Coordinating center

##### Location

The study is conducted in the Acharya Vinoba Bhave Rural Hospital’s Obstetrics and Gynaecology Ward at the Datta Meghe Institute of Medical Sciences in Sawangi (Meghe), Wardha, Maharashtra, India.

##### Role

Subject recruiting, eligibility screening, randomization, intervention delivery, data collection, and data administration.

#### Trial steering committee

The principal investigator is in charge of participant enrollment, randomization, assignment to intervention groups, and overall study conduct.

Physician oversees participant safety, handles unfavorable outcomes, and reports to the institutional ethics committee.

The Ethical Committee oversees ethics and examines reports of undesirable events.

### Composition of the data monitoring committee, its role, and reporting structure {21a}

#### Safety monitoring

Throughout the trial, the lead physician keeps an eye on, assesses, and handles any unintended consequences or adverse occurrences.

#### Reporting

The Institutional Ethical Committee is notified of any unfavorable occurrences for additional monitoring and, if required, action.

#### Ethical oversight

The Institutional Ethical Committee makes sure that the trial is carried out in accordance with ethical guidelines and that subject safety is preserved.

### Adverse event reporting and harms {22}

The physician in charge of evaluating and managing inadvertent and requested adverse events, as well as any other unanticipated results of trial interventions or trial conduct, shall be informed of every adverse event that takes place. The reports will also be sent to the ethical committee.

### Frequency and plans for auditing trial conduct {23}

Not applicable.

#### Rationale

Because of the non-invasive procedures, the study can be regarded as low risk and a small sample size, which lessens the need for official auditing.

